### Objectives

The objectives of the study are to evaluate the effectiveness of the minimally guided MindNotes app in enhancing professional help-seeking behaviors among individuals with self-reported common mental health concerns and significant psychological distress who are not currently engaged in treatment. Additionally, the study aims to examine the utility of this app in improving the inclination to seek help from mental health professionals, reducing perceived barriers to seeking professional help for mental health, reducing psychological distress, and documenting perceived benefits of using the app. Help-seeking behavior is the primary outcome variable, while help-seeking inclination, barriers to seeking professional help, and psychological distress are the secondary outcome variables.

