### Power Calculation

A sample size of 150 participants per group has been estimated based on detecting a difference in help-seeking behavior (25% vs 10%) with 80% power at a 5% significance level using G*Power 3.1, allowing for up to 33% attrition commonly observed in minimally guided digital interventions [26]. These include interventions delivered through digital platforms, which often vary widely in design and outcomes. Consequently, closely comparable studies for precise sample size estimation were difficult to identify, and the current estimate is informed by findings from studies with broadly similar characteristics [14,27].

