### Procedure

Participants will be randomized into either the intervention or control group in a 1:1 ratio, using a computer-generated randomization sequence. The randomization list will be generated by the study supervisor. Stratified randomization will be used based on age group (18-35 years and 36 years and above) and gender to ensure balance across key demographic variables.

A brief telephonic interview for eligibility screening will be conducted after all other questionnaires are completed. This call allows the researchers to clinically assess the current mental state and amenability to take part in the study process, inquire whether participants have sought consultation for any psychiatric problem in the past or recent times, and confirm willingness to participate.

Eligible participants will receive an introductory call informing them of their group allocation and guiding them on how to begin engagement with the study activities. All assessments will be conducted through an online survey, and feedback will be obtained over the phone from both groups at the end of the 4-week intervention period. A follow-up telephonic interview will be conducted 1 month after the postintervention assessment to ascertain help-seeking inclination and help-seeking behavior. The flow of the study is depicted in Figure 1.

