Suicidal ideation—2 brief items developed for the study will be used to determine significant suicidality based on frequency and controllability. This is for screening out those who may need immediate support and referral. The first item asks, “In the past month, how often have you had thoughts about suicide?” with response options ranging from never (coded as 1), rarely or 1-2 times (coded as 2), sometimes (coded as 3), often (coded as 4), and all the time (coded as 5). The second item asks, “When feeling very sad or emotionally distressed, and thoughts of self-harm or suicide arise, how much control do you feel you have over acting on these thoughts?” Responses are rated as able to control easily (coded as 1), able to control with some difficulty (coded as 2), able to control with great difficulty (coded as 3), not able to control (coded as 4), and not applicable—do not experience such thoughts (coded as 5). All participants who report rarely having suicidal thoughts with great difficulty or no control; those who report sometimes having suicidal thoughts with great difficulty or no control, or those reporting often having suicidal thoughts, regardless of how much control they report, will be excluded.

Help-seeking inclinations will be assessed through the use of the General Help-Seeking Questionnaire (GHSQ). This 14-item scale will be used to assess the likelihood of seeking help from various sources (eg, parents, friends, helpline, and mental health professionals) for current mental health concerns or psychological distress, on a 7-point Likert scale [32]. Ratings on the item specific to mental health professionals will be the primary focus, although help-seeking inclination from various sources will also be documented. At follow-up, for the sake of minimizing respondent burden, help-seeking inclination only from mental health professionals will be assessed using the corresponding GHSQ items with a 7-point Likert-type scale.

The Barriers to Seek Professional Help for Mental Health Scale (BSPH-MHS) will be used to assess the severity and nature of perceived barriers to professional help-seeking for mental health concerns or psychological distress. It is a 28-item, 5-point Likert scale that evaluates perceived barriers across 4 domains: distress perception, stigma, service apprehensions, and instrumental obstacles with previous research supporting its reliability, construct, and convergent validity [30].

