### Ethical Considerations

The study has been approved by the Institutional Ethics Committee of the National Institute of Mental Health and Neurosciences, Behavioural Science Division (NIMHANS/45th IEC [BEH.SC.DIV.]/2024/22.03.2024) and is prospectively registered in the Clinical Trials Registry of India. Informed consent will be obtained from individuals prior to recruitment, and no compensation will be offered to participants for taking part in the study. Baseline and postintervention surveys will be administered electronically via REDCap (Research Electronic Data Capture), a secure, web-based platform for data collection and management, hosted at the first author’s institution. The digital apps used in the study incorporate “privacy by design” and use technical and policy safeguards to ensure the security of the data and protect the privacy of users. User passwords are stored securely through encryption. Personally identifiable information elements (email addresses and phone numbers) are stored in encrypted form and are decrypted within the program when needed. The data obtained from the participants through text messages and emails will be backed up and stored on a password-protected system.

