### Data Analysis Plan

Quantitative analyses will be conducted using SPSS Statistics (version 31.0; IBM Corp). Baseline characteristics will be summarized descriptively. Differential attrition will be examined by comparing dropout rates between groups using chi-square tests and by assessing baseline differences between completers and noncompleters using appropriate statistical tests. Sensitivity analyses will be conducted as needed based on the observed pattern of missing data.

Occurrence of professional help-seeking at the postintervention assessment and follow-up will be compared between groups using proportions, chi-square tests, and odds ratios with 95% CIs, with Cohen *h* reported as the effect size. As this behavioral outcome has no baseline variation in the nontreatment-seeking study sample, this will be treated as a completer analysis involving participants who provided postintervention assessment data.

For continuous outcomes, linear mixed-effects models will be used to estimate group, time, and group×time effects under an intention-to-treat framework. In addition, completer-only analyses will be conducted as exploratory comparisons to describe observed change among participants with complete data. A 2-sided significance level of .05 will be used.

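### The mixed models for the continuous secondary outcomes leave the arms free to differ at baseline, which costs some precision that adjusting for baseline would recover

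*Protocol article*

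**What the plan says.** The Data Analysis Plan names the fixed effects for continuous outcomes: "linear mixed-effects models will be used to estimate group, time, and group×time effects", within an intention-to-treat framework. It mentions no baseline covariate and no constraint that the arms share a baseline mean. The Objectives section identifies the outcomes concerned: "help-seeking inclination, barriers to seeking professional help, and psychological distress are the secondary outcome variables". The test level is given as follows: "A 2-sided significance level of .05 will be used".

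The number of time points per scale follows from three other places. Ethical Considerations says: "Baseline and postintervention surveys will be administered electronically via REDCap". Procedure says of the later contact: "A follow-up telephonic interview will be conducted 1 month after the postintervention assessment to ascertain help-seeking inclination and help-seeking behavior". Data Collection Instruments adds that at follow-up "help-seeking inclination only from mental health professionals will be assessed using the corresponding GHSQ items". So K10 and BSPH-MHS have two time points, and only the GHSQ item on mental health professionals has three.

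**The concern.** With two time points, a time effect for K10 or BSPH-MHS can be estimated only if baseline is among the responses. The group main effect is then the arm difference at baseline. Under 1:1 randomisation its expected value is zero, so the model spends information on a quantity that the design already fixes.

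With complete pairs, the group×time effect is exactly the difference between arms in mean change. A chance imbalance at baseline is then subtracted in full, whereas the efficient correction is in proportion to how well baseline predicts the later score. The result is a wider confidence interval for inclination, barriers and distress.

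This matters in practice because Strengths and Limitations accepts that inclination may improve without a change in behaviour within the follow-up period. If the primary result is null, the precision of these secondary estimates will carry much of the interpretation.

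**Working it through.** **Inputs from the article.** The sample size is based on "detecting a difference in help-seeking behavior (25% vs 10%) with 80% power at a 5% significance level", with 150 per group and up to 33% attrition (Power Calculation). Allocation is 1:1 (Procedure). Entry requires K10 of at least 20 (Recruitment and Sampling).

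**Assumed.** The baseline-post correlation r, equal SDs at the two times, and missingness at random. None of these is given in the article.

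**Plan's own figure.** Two proportions, pooled variance under the null: [1.96√(2×0.175×0.825) + 0.8416√(0.25×0.75 + 0.10×0.90)]² / 0.15² = (1.053 + 0.443)² / 0.0225 ≈ 99.5, so 100 per arm. Then 100/0.67 = 149.3, so 150. The stated figure reproduces. It gives n = 150 randomised and m = 100 observed per arm.

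**Variance of the estimated arm difference, in SD² units.**
- Change score, m complete pairs per arm: 4(1−r)/m.
- Baseline-adjusted (ANCOVA or common baseline mean): 2(1−r²)/m.
- Planned model, baseline on n and postintervention on m per arm: 2[(1−r²)/m + (1−r)²/n].

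The ratio of adjusted to planned variance is (1+r)/2 with complete data. With attrition it is (1+r)/[(1+r) + (m/n)(1−r)], where m/n = 2/3. At r = 0.5 this is 1.5/(1.5 + 0.333) = 0.818.

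| r | Complete data: variance saved | Planned CI wider by | 33% attrition: variance saved | Planned CI wider by |
|---|---|---|---|---|
| 0.4 | 30% | 20% | 22% | 13% |
| 0.5 | 25% | 15% | 18% | 11% |
| 0.6 | 20% | 12% | 14% | 8% |
| 0.7 | 15% | 8% | 11% | 6% |
| 0.8 | 10% | 5% | 7% | 4% |

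At r = 0.5 with 100 observed per arm, the 95% CI half-width is 0.240 SD adjusted, 0.265 SD under the planned model and 0.277 SD for a completer change score. The planned model lies between the other two because it keeps the baselines of those who drop out.

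**Simulation check** (r = 0.5, 150 per arm, 300 runs, random-intercept model). With complete data the group×time estimate equalled the difference in mean change to within 5×10⁻¹⁵. Its mean SE was 0.115, against 0.100 for ANCOVA. With one third of postintervention values missing at random, the mean SEs were 0.135 (planned model), 0.141 (change score) and 0.123 (ANCOVA).

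**K10.** The entry cutoff shrinks the baseline variance to a fraction k, so subtracting baseline adds less noise. Assume a slope of 0.6 (untruncated r = 0.6, equal SDs before selection). The residual variance is then 0.64, and the extra term is (1−0.6)²k = 0.16k. For a truncated normal, k = 1 + αλ − λ², with α = (20 − mean)/SD and λ = φ(α)/[1 − Φ(α)].

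For mean 25 and SD 8: α = −0.625, λ = 0.328/0.734 = 0.447, k = 0.521. The complete-data ratio is 0.64/(0.64 + 0.083) = 0.885. With attrition it is 0.64/(0.64 + ⅔×0.083) = 0.920.

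Across assumed pre-selection distributions of (mean 22, SD 8), (25, 8) and (28, 7), complete-data ratios from 2,000,000 simulated draws are 0.904, 0.885 and 0.857, a saving of 10% to 14%. Applying the factor 2/3 to the extra term gives ratios of about 0.93, 0.92 and 0.90, a saving of 7% to 10%.

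**The case against.** The strongest reply is that group, time and group×time is a standard and valid longitudinal specification, that randomisation keeps its interaction estimate unbiased, and that only secondary outcomes are touched. All of that stands. It limits the point to efficiency.

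A second reply is that a condensed article leaves model details to an analysis plan. That holds for the covariance structure and the reported contrast. It is weaker here, because the article does name the fixed effects, including a group effect, and the assessment schedule forces baseline into the outcome vector for K10 and BSPH-MHS.

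A third reply concerns size. A reader might infer that the planned model is simply a change-score analysis and that 20% to 30% of the variance is wasted. The documents do not support that reading. The reduction is exact only with complete pairs, whereas the article allows for up to 33% attrition and places the model in an intention-to-treat framework, so dropouts' baselines contribute. The attrition columns are the ones to use, and the loss shrinks further as r rises.

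A reader might also infer that these outcomes are meant to explain how the app works, so that the loss undermines a mechanism analysis. The article lists them only as secondary outcomes and describes no mediation analysis. Nor is the absence of a power statement for secondary outcomes a fault.

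**Conclusion.** The point holds as an avoidable loss of precision on the continuous secondary outcomes. With the planned attrition, the variance saving is about 22%, 18% and 14% at r = 0.4, 0.5 and 0.6, and about 7% to 10% for K10. At r = 0.5, the saving equals the information from about 22% more participants (1/0.818 = 1.22).

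These figures rest on an assumed r, on equal SDs, on missingness at random and, for K10, on an assumed distribution before the cutoff. The loss vanishes only if the slope of the later score on baseline is 1. The GHSQ professional item does not escape: with time as a category and complete data, each group×time contrast against baseline is still a difference in change.

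The point should not be read as a claim of bias or of an invalid analysis. The primary outcome is binary with no baseline variation, and it and the 150 per group are unaffected. The change is worth making because it is free.

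**What to change.** Prespecify one baseline mean for both arms. In the mixed model, code time as a category and add treatment indicators only at postbaseline times, with no treatment term in the baseline cell, and use an unstructured covariance.

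Deleting the group main effect while keeping the full categorical group×time interaction is not enough. Those terms still give each arm its own baseline mean, so the same model is refitted. In SPSS the indicators therefore have to be built explicitly.

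An alternative is to model the postbaseline scores with the baseline score as a covariate, which is ANCOVA for K10 and BSPH-MHS.

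In either form, include the stratification factors age group and gender. Report the arm difference at postintervention for K10, BSPH-MHS and the GHSQ professional item, and at follow-up for the GHSQ professional item.

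The cost is a short change to the model specification, with no new data and no change to the sample size. It should be recorded before outcome data are examined. The trial is unblinded with self-reported outcomes, so choosing baseline adjustment after seeing results would be open to challenge. The article expects data collection to run to July 2026.

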## Results

The study is part of a project funded by the Indian Council of Medical Research. The funding for the project was received in May 2024. The study was initiated in September 2025. Data collection is expected to be completed by July 2026. The results of the study are expected to be published by December 2026.

## Discussion

### Anticipated Findings

The minimally guided MindNotes app represents an innovative approach to addressing the mental health needs of individuals experiencing psychological distress but who may be uncertain or ambivalent about seeking professional help. This trial seeks to evaluate the app’s effectiveness in enhancing help-seeking, a factor that remains crucial in bridging the treatment gap in low-resource settings such as India [3,15]. In addition, reductions in perceived barriers to help-seeking and psychological distress will be examined because the intervention app includes components directed at learning self-help skills to deal with common mental health concerns, as well as simple tips and strategies to identify and overcome one’s hesitations to seek professional help when needed.

Previous research has highlighted the promise of digital interventions in increasing engagement with mental health care, particularly through the use of behavioral nudges and minimal guidance strategies [14,27]. Building on this evidence, this study tests the combined use of a structured, self-help mobile app with strategically spaced, personalized, and generic reminders. This integrated design is intended to address 2 common challenges in digital mental health interventions: user engagement and retention [33]. The trial is currently in its preliminary phase, with participant recruitment underway. It is anticipated that the study will provide valuable insights into the effectiveness of a minimally guided app-based intervention for hard-to-reach, distressed, nontreatment-seeking individuals in the community [27]. The intervention specifically targets nontreatment-seeking individuals, a group often underserved and unreached by conventional mental health care systems and seeks to evaluate their response to digital support aimed at enhancing mental health awareness, self-help, and help-seeking.

### Strengths and Limitations

The study follows a randomized controlled trial approach, which adds value to the methodological rigor and ensures reliable findings. From an ethical perspective, having an active control group ensures that no participant with distress is denied mental health support. The component of minimal guidance is an advantage of this study as it helps keep participants engaged. Nevertheless, the proposed study has a few inherent limitations. To reach distressed nontreatment seekers, it invites participation from those experiencing psychological distress but not accessing professional help. This approach is likely to appeal to individuals who are ambivalent or in the contemplation stage of seeking help. While the intervention may assist in resolving such ambivalence and encourage movement toward actual help-seeking behavior, those with very limited awareness of their mental health concerns—those in the precontemplation stage—may not be reached. Blinding will not be feasible in this study since the participants will be aware of the nature of the intervention they engage with, and the outcome measures are based on self-reports (eg, help-seeking). It is plausible that while participants’ inclination to seek help may improve, this may not translate into actual professional help-seeking behavior within the 1-month follow-up period. Moreover, help-seeking behavior is influenced by access to affordable professional services (supply-side factors) and other logistical constraints. Although the study will aim to provide appropriate guidance and refer interested participants to relevant local resources, these measures may not always be sufficient to initiate professional help-seeking behavior. Finally, while sustained engagement with mental health services is a key factor in achieving longer-term clinical outcomes, examining the quality of care received or satisfaction with professional consultations falls beyond the scope of this study.

### Future Directions

Limitations of the study notwithstanding, it is expected to make a meaningful contribution to the growing body of literature on mobile mental health interventions in low- and middle-income countries. By leveraging an accessible, scalable, and low-cost indigenous platform, digital interventions such as MindNotes hold promise as viable public mental health strategies in urban Indian community settings, empowering individuals through guided self-help and improving timely help-seeking, particularly when complemented by enhanced access to professional services.

### Conclusions

If proven effective, the study may inform future design, delivery, and policy integration of similar digital tools, helping to address demand-side barriers that contribute to the persistent treatment gap for common mental health concerns in India.

## Abbreviations

BSPH-MHS: Barriers to Seek Professional Help for Mental Health Scale
GHSQ: General Help-Seeking Questionnaire
K10: Kessler Psychological Distress Scale
REDCap: Research Electronic Data Capture
SPIRIT: Standard Protocol Items: Recommendations for Interventional Trials
